**1.5. Potential effect of IPTi on clinical immunity**

A potential negative influence of IPTi on clinical immunity to malaria, which is normally acquired naturally as the consequence of repeated *P. falciparum* infections, remains an import question. This might lead to a rebound effect on malarial morbidity with an increased incidence of mild or severe malaria in the second year of life, despite the beneficial effect of IPTi on the burden of disease during the first 12 months. Protective immunity has been shown to be mediated, at least partly, by the acquisition of agglutinating antibodies against parasite-encoded, variant-specific antigens on the surface of infected red blood cells, the variant surface antigens.33,34 Protection is related to the acquisition of a broad repertoire of anti-VSA antibodies, and antibodies against a specific subset of parasite antigens that are particularly well expressed during infections in young children have been shown to be related to protection from severe disease during the first few years of life.35-37 Studies have further shown that asymptomatic low-density parasitaemia in children in itself is linked to a lower incidence of uncomplicated malaria.38 Together, these findings point to the importance of asymptomatic,low-grade parasitaemia in the induction of protective anti-VSA antibodies during infancy, particularly against severe forms of disease; a protection that may be disrupted by a repeated clearance of parasitaemia by presumptive intermittent treatment. Thus, it is important to assess the interaction between IPTi and the development of clinical immunity in children.

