**2.1 Co-primary objectives**

This study has four main objectives

- Identification of a drug that could be used safely and effectively for IPTi instead of SP in areas, such as north eastern Tanzania, where there are high levels of resistance to SP and amodiaquine.
- Determination of whether a short acting antimalarial drug (Lapdap) is as effective as a long acting drug (mefloquine) when used for IPTi.
- Investigation of the effect of the intensity of transmission on the requirements for a long or short acting drug for IPTi.
- Assessment of the effect of IPTi on the development of clinical immunity in children in low and high transmission areas.

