**4.3. Outcome measures**

*Primary outcome measures*

1. Incidence of clinical malaria: [(history of fever during previous 2 days or axillary temperature >37.5ºC) + parasitaemia of any density + absence of any other obvious causes of fever] during the period of 2-11 months of age

*Secondary outcome measure*

1. Mean Hb at 10-12 months of age (one month after the third course of IPTi)
2. Incidence of severe anaemia (Hb <7 g/dl) during the period of 2-11 months of age
3. Prevalence of parasitaemia at 10-12 months of age (one month after the third course of IPTi)
4. Incidence of clinical malaria [as defined above] during the period of 12-23 months of age.
5. Level and repertoires of plasma antibodies to *plasmodium falciparum* variant surface antigen (anti-VSA antibodies) at 10 and 18 months of age.
6. EPI serology
7. Prevalence of G6PD deficiency and human haemoglobinopathies.

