# Change in Contact 7 for Low transmission site

Contact 7 at age 18 months will be the last scheduled visit for children at the low transmission site. This is because the low incidence in malaria at the site means that there is a very small chance that this study will detect a rebound effect of malaria even if present.

At the high transmission site, all children will be invited to attend the clinic at the age of approximately 24 months (**contact 8**) and finger prick blood sample will be obtained for screening for malaria using Paracheck dipsticks and also for preparation of blood slides, filter paper samples and Hb. If a child is positive dipstick test is currently febrile (Temp >37.5° C) or has a history of fever with in the past 2 days, and/or has a history of taking SP for a febrile illness during the previous week, the child will be treated with Artemether - Lumefantrine.

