**Anti-VSA antibody assays**: Anti-VSA antibodies will be measured with a flow cytometric assay that allow the assessment of levels of plasma antibodies to a panel of *in vitro* cultured parasite isolates, some of which are commonly and others rarely recognized. Further antibody assays will be used including ELISA and adhesion-blocking assays. Levels of antibodies and the proportion of parasites recognized will be compared between treatment groups and analysed with respect to clinical protection with statistical regression models. We will compare the level and repertoire of anti VSA antibodies at 10 and 18 months of age, and the incidence of malaria in the second year of life between the study arms. We will include the following terms in a Poisson regression model to assess the effect to IPTi on immunity and clinical malaria: IPTi regime, level of anti VSA antibodies, age, sex, transmission levels and other potential confounders identified during the analysis as predictors and incidence of malaria as the outcome.

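### The Poisson model said to assess the effect of IPTi adjusts for anti-VSA antibody, a post-randomisation outcome and hypothesised mediator, so its IPTi coefficient need not be the total effect of IPTi

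*Protocol*

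**What the plan says.** The fourth co-primary objective (section 2.1) is "Assessment of the effect of IPTi on the development of clinical immunity in children in low and high transmission areas". Section 1.5 gives the reason. Anti-VSA antibody is described as part of protective immunity, induced by low-grade parasitaemia, and the result is "a protection that may be disrupted by a repeated clearance of parasitaemia by presumptive intermittent treatment". The feared consequence is more malaria in the second year of life.

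The anti-VSA paragraph of section 4.12 then plans two things.

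- Between-arm comparisons: "We will compare the level and repertoire of anti VSA antibodies at 10 and 18 months of age". The same sentence extends the comparison between arms to malaria incidence in the second year.
- A regression: "We will include the following terms in a Poisson regression model to assess the effect to IPTi on immunity and clinical malaria". The terms are "IPTi regime, level of anti VSA antibodies, age, sex, transmission levels and other potential confounders identified during the analysis as predictors", with "incidence of malaria as the outcome".

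Section 4.3 lists anti-VSA level and repertoire at 10 and 18 months as a secondary outcome. Second-year malaria is a separate secondary outcome, counted "during the period of 12-23 months of age". Section 6 says malaria incidence will be analysed by Poisson regression and names no antibody term.

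**The concern.** The regression is given a purpose that it cannot serve. Randomisation makes the arms comparable at the time of allocation. Antibody at 10 or 18 months is measured after dosing has started, and the protocol itself proposes that dosing may change it. Holding antibody fixed while comparing arms removes whatever part of the IPTi effect runs through antibody, and that is the part the objective asks about. Because malaria is the outcome, the model also cannot estimate an effect on immunity.

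Antibody reflects past exposure as well as protection. Conditioning on it can therefore leave the arms unbalanced on exposure, in which case the coefficient is not a clean direct effect either.

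The practical risk is one of interpretation. If IPTi does cause rebound through lost immunity, the model labelled as assessing the IPTi effect would show a weakened effect or none, and the distortion would be greatest when the safety hypothesis is true. The plan would then hold two answers to one question and would have attached the IPTi-effect label to the less suitable one.

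**Working it through.** **The plan's own second-year figures.** Table 6b takes 0.62 for placebo and 0.86 for mefloquine at 12-23 months (footnote: a 40% increase) and gives 59 per arm. The two-proportion formula with two-sided 5% significance and 80% power gives

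n = [1.96 × √(2 × 0.74 × 0.26) + 0.842 × √(0.62 × 0.38 + 0.86 × 0.14)]² / 0.24² = 51.2,

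and the continuity correction gives 51.2/4 × [1 + √(1 + 4/(51.2 × 0.24))]² = 59.3. The planned figure is reproduced (60 if rounded up). The point does not rest on it; it only confirms which second-year effect the plan had in mind.

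**Timing, from the text.** The first course is given at about 2 months and the third at about 9 months. Antibody is sampled at about 10 months (one month after the third course) and at 18 months. Both samples follow the start of dosing. The 10-month sample precedes the 12-23 month window. The 18-month sample falls inside it, with months 12-17 (6 of 12) already past.

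**Size of the mediation effect.** Inputs from the protocol: true total rate ratio 1.40, baseline rate 0.62, 320 per arm. Assumptions, none of them in the protocol: each SD of antibody multiplies the malaria rate by 0.67 (log −0.40), and a share s of the IPTi effect passes through antibody.

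- Total log rate ratio: ln 1.40 = 0.3365.
- Antibody shift needed: a = −s × 0.3365/0.40, which is −0.84 SD when s = 1.
- IPTi rate ratio with antibody in the model: exp[(1 − s) × 0.3365].

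Simulated Poisson regressions (400 replicates per row) agree with the formula:

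| Share through antibody | No antibody term | Antibody term, formula | Antibody term, simulated | Antibody term, shared exposure added |
|---|---|---|---|---|
| 0% | 1.41 | 1.40 | 1.41 | 1.41 |
| 25% | 1.40 | 1.29 | 1.29 | 1.36 |
| 50% | 1.40 | 1.18 | 1.18 | 1.32 |
| 75% | 1.40 | 1.09 | 1.09 | 1.27 |
| 100% | 1.39 | 1.00 | 1.00 | 1.24 |

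The last column assumes an unmeasured exposure that correlates 0.5 with antibody and raises the log malaria rate by 0.5 per SD. The antibody coefficient then becomes −0.40 + 0.5 × 0.5 = −0.15 (rate ratio 0.86). With full mediation the IPTi log ratio is 0.3365 − 0.84 × 0.15 = 0.21, a ratio of about 1.23 (1.24 simulated). That is neither the total effect (1.40) nor the direct effect (1.00). Without the antibody term the simulated ratio was 1.39 to 1.41 in every scenario.

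**Size of the timing effect, 18-month sample only.** Suppose each episode at 12-17 months raises the 18-month antibody by 0.7 SD (assumed). A truly protective antibody ratio of 0.67 is then estimated as 1.00. The IPTi ratio stayed near 1.40 in that scenario, but only because of the values chosen.

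**The case against.** The strongest reply is that the total effect is already planned. The sentence before the regression compares antibody and second-year malaria between arms, and the Poisson analysis in section 6 names no antibody term. A real rebound would show there. This stands. A reader might infer that the antibody-adjusted model is the only analysis serving the fourth objective, or that a rebound would go unseen. The documents do not support either.

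Second, fitting arm and antibody together is an ordinary way to study mediation or correlates of protection, and section 4.12 does say that antibody will be analysed in relation to clinical protection. This also stands. What fails is the stated purpose, which is to assess the effect of IPTi.

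Third, antibody is not randomised, so confounders of the antibody-malaria association have a proper place in the joint model. That is right. The objection to covariates found during the analysis applies only to an estimate of the arm effect.

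Fourth, two stronger readings are tempting. One is that IPTi does lower antibody; section 1.5 says only that it may. The other is that the 18-month value will be used; the text does not say, and the 10-month value would avoid the overlap with the outcome window. The choice of sample could be left to the detailed analytical plan promised in section 6. The purpose given to the model is already fixed in the protocol.

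**Conclusion.** The point holds as a mis-specified purpose. As written, the model's IPTi coefficient is at best the part of the effect that does not pass through antibody, and with shared exposure it may not be even that. The model cannot measure an effect on immunity.

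The size is illustrative. With a true ratio of 1.40, adjustment gives anything from 1.40 (nothing mediated) down to 1.00 (all mediated, no shared exposure). The strength of antibody protection, the mediated share, the exposure correlation and the boost per episode are all assumptions, and the protocol supports no particular value. The distortion disappears if IPTi leaves antibody unchanged. Reverse causation applies only if the 18-month sample is used.

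A reader might infer that the trial's main result is at risk. It is not: the primary outcome, malaria at 2-11 months, does not depend on this model. Nor does the working show a spurious rebound being created; with no true effect, the one case run (18-month antibody boosted by episodes) gave an IPTi ratio of 1.00.

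**What to change.** Reword the anti-VSA paragraph of section 4.12, and carry the wording into the analytical plan before the codes are broken:

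1. The effect of IPTi on second-year malaria is estimated from the between-arm comparison, in a model with arm, site and pre-randomisation covariates only. It has no antibody term and no covariates chosen during the analysis.
2. The effect of IPTi on immunity is estimated by comparing antibody level and repertoire between arms at 10 and 18 months.
3. The model with both arm and antibody is labelled an exploratory mediation or correlate-of-protection analysis. It uses the 10-month antibody and counts malaria only after that sample. Confounders of the antibody-malaria association may be included there.

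The cost is analysis wording only. No new data, visits or participants are needed.

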**5. Monitoring of the trial**

The trial will be conducted under conditions of good clinical practice (GCP), following as closely as possible the ICH guidelines. Standard operating procedures (SOPs) will be developed for all major operations. A DSMB will be established to look after the trial. Members will include an experienced clinician, a statistician and a person with local knowledge of the study area. Discussions will be held with the DSMB prior to the start of the trial to identify their requirements for adverse events reporting and these will be met. The DSMB will also be consulted about the advisability of an interim analysis, in particular for the SP group as this drug may prove to be ineffective.

At each study site, a local physician will be assigned to be the local safety monitor. He or she will have access to the codes of the study drugs. All serious adverse events will be reported to the local safety monitor by the project physician. In the event of a serious adverse event associated with a study drug, the local safety monitor will be empowered to break the code for that child and, if it is considered necessary to temporarily suspend the trial, prior to discussion with the DSMB.

It is proposed that a clinical monitor will be appointed by the IPTi consortium to monitor all the trials conducted under its auspices and it is anticipated that the monitor will visit the study site on at least one occasion during the trial and provide advice that will help to ensure that the study is conducted to the highest clinical standard.

1. **Data management and analysis**

Data will be entered twice into a database using access software. The accuracy of data input will be checked and validated using a customized validation programme. The comparison of the incidence of malaria and severe malaria will be analysed using Poisson regression models. The statistical significance of differences in mean Hb will be assessed using t-test. We will consider the trials in the low and high transmission areas as separate and we recognise that trials is not adequately powered to make a direct comparison of the effects in the two areas.

There will be two comparisons which are relevant with respect to multiple comparison, Lapdap vs Placebo and SP vs Placebo, and Mefloquine vs placebo will be the primary comparison. As we expect the effects of the two drugs to be similar, it would not be appropriate to power the trial on the Lapdap vs SP comparison. If we make two comparisons at the .025 level of significance then, under the null hypothesis, there is a .05 probability that one will be significant by chance. However we argue it would be appropriate to conduct one-sided tests, on the basis that there is no mechanism by which those given the active drug would have more malaria in the first year than those who do not.

We considered the possibility of powering the study at the 0.025 significance level rather than 0.05 level to allow for an excess of malaria in the first year of life among those on the active drugs in order to get over issue of the multiple comparisons. This would require increasing the sample size by 20%. This would mean increasing the number of infants in the low transmission are from 2200 to 2600 and in the high transmission areas from 1200 to 1440. This would require prolonging the study by four months. Thus,

we have opted to keep the power of the study at 0.05 level for the following reasons: (1) an enhanced incidence of malaria during the first year of life while on an active drug is very unlikely and so we can use a one-sided test (2) enrolling an additional 640 infants would increase substantially the logistical complexity and cost of the study but the added value of this would be small.

A detailed analytical plan will be prepared and submitted to the DSMB before the study drug codes are broken.

1. **Dissemination of results**

The nature of the trial and its possible implications will be discussed with the national Malaria Control and EPI programmes before the start of the trial. On completion of the study, results will be presented to the communities where the trial was undertaken, to local health authorities and to the National Malaria Control programme as well as in the international scientific press.

1. **Ethical considerations**

Giving placebo to infants in one arm of the study is needed for the following reasons: (1) although IPTi with SP has been shown to be beneficial in an area with low transmission, high bednet use, and low SP resistance, there is no clear evidence that IPTi with SP will be beneficial in area with high transmission and high SP resistance; (2) a placebo arm is essential for assessing any interaction between mefloquine and measles vaccine. Study infants will be monitored closely and if they develop clinical malaria they will be identified and treated promptly.

Giving SP to one arm of the study, even though we anticipate that there will be high level of SP resistance in the study area is justified on the grounds that (1) some infants in this arm will benefit from IPTi; (2) as these infants are asymptomatic, there is not imminent danger of progression to clinical malaria. Study infants will be monitored closely and if they develop clinical malaria they will be identified and treated promptly.

Giving mefloquine to one arm of the study is justified as this is the most suitable alternative drug to SP which has a long duration of action and which can be given as a single dose. Mefloquine needs to be used with caution in infants of less than 3 months of age. However, side effects with this drug are rare events and may be balanced by the ability of IPTi with mefloquine to reduce the burden of malaria in infants in areas with SP resistance. Mefloquine is widely used in the private sector for treatment of malaria, including infants, in Tanzania.

Lapdap has been shown to be safe in infants and it is envisaged that this drug will be used widely in Africa in the future.

Collecting blood samples causes minor discomfort. However, the results of this blood examination will be used to offer appropriate treatment. The MoH of Tanzania offers free treatment for children. The project has earmarked a budget for drugs if there is a shortage of drugs for treatment of study children.

Prior to the start of the study the nature of the trial will be discussed with the study population at a series of village meetings. Details of the trial will be discussed with health and civil authorities in the study area. The benefits and risks of taking part in the study will be explained to caretakers at an individual level and their written consent will be obtained before enrolling infants into the study. Approval for the study will be obtained from the ethics committees of Tanzania and the LSHTM

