**Figure1: Parasite prevalence in the Kilimanjaro region**

[figure not shown]

Source: Drakeley C, Reyburn et al. MIM conference abstract no. 318, Arusha, Tanzania

malariometric survey in 2002 showed significant variation in the prevalence of malaria parasitaemia in <5 year old children at different levels of altitudes within and between the

districts (Figure 2). The survey was conducted in four groups of villages: Rombo (purple), South Pare (pink), Western Usamabara (yellow) and Eastern Usambara (grey). The relationship between the mean altitude of the village and the prevalence of parasitaemia is shown in the graph (insert). The mean altitude of villages within in each group ranged from 200 to 1800 meters. The prevalence of malaria parasite in 0-4 year old children ranged from 20% to 55% in the lowlands (<750m) and from 1% to 20% at 1000-1500m altitude. The malaria transmission pressure in lowland villages in the South Pare district is low/moderate. The prevalence of malaria parasitaemia was 30% in 1-4 year-old children and 4% in <1 year-old infants. The prevalence of parasitaemia was higher in Western Usambara villages (52% in 1-4 year-old children and 20% in <1 year-old infants).

The advantages of the study site for the proposed trial are:-

1. Levels of resistance to SP and amodiaquine are high and so investigation of alternative drugs that could be used for IPTi is needed urgently and can be justified ethically.
2. A wide range of levels of malaria transmission are found over a small area in a homogeneous population.
3. The epidemiology of malaria in the study area has recently been carefully defined.

Although detailed epidemiological studies have recently been undertaken in the study area, it will be necessary to confirm that major differences persist between highland and lowland sites during the period of the trial. We have considered the possibility of making direct measurements of EIR but this is difficult and expensive in low transmission areas because of the paucity of anopheline mosquitoes and the low sporozoite rate. In a recent study in Hai district, Tanzania, 2198 anopheline mosquitoes were collected over a period of 12 months and only 8 mosquito were infected giving an EIR with very wide confidence limits. Instead of EIR estimates, we will rely upon the prevalence of infection in nine month old infants in the placebo groups to estimate the force of infection in the two sites.

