**Figure 2**. **Study design**

**Contact 0**: Infants attend EPI clinics for BCG and/or DPT & Polio1 vaccines

1. identification of eligible infants

2. provision of information about the study to the care takers

3. enrolment of eligible infants after obtaining informed consent

2 months

Approximate age

**Contact 1:** Infants return for DPT 2 and Polio 2 vaccines

1. random allocation to one of the study groups

2. administration of the first course of treatment

3. collection of blood samples for Hb and blood film and filter paper

4. appointment for contact 2 (DPT and polio 3)

Group 1

placebo

Group 2:

Mefloquine

Group 3:

Lapdap

Group 4:

SP

Passive surveillance at health facilities for side effects of drugs, clinical malaria, and anaemia until 24 months of age

**Contact 2**: Infants attend EPI clinic for DPT 3 & Polio 3 vaccines

1. completion of data forms and administration of the second course of allocated drug

2. appointment for contact 3 (measles vaccine)

**Contact 3**: Infants attend EPI clinic for measles vaccine

1. completion of data forms and administration of the third course of allocated drug
2. collection of blood samples for baseline measles serology
3. appointment for contact 4 (1 month after the date of contact 3)

**Contact 4**: (1 month after the date of contact 3)

Collection of blood samples for Hb, blood film, post vaccine measles serology, and anti-VSA antibody assay

1 months

3 months

9 months

10 months

**Contact 5**: (20% random sample)

Collection of blood sample for Hb and blood film

**Contact 6**: (20% random sample)

Collection of blood sample for Hb and blood film

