All study infants will be encouraged to attend the study health facilities for any illness. At these visits a health questionnaire will be completed and temperature recorded using an electronic thermometer. A finger prick blood sample will be collected for Hb and malaria parasite and for detection of molecular markers of resistance from all infants attending the study health facilities for any illness that is clinically diagnosed as malaria. At the health centres one blood slides will be examined on the same day for deciding on appropriate treatment whilst the second slide will be read in the central laboratory to provide definitive diagnosis.

Children with proven or presumptive malaria will be treated according to the MoH guidelines for managing treatment failures following first line drugs. We have opted for the second line antimalarials instead of giving SP, the first line drug recommended by the MoH, because we believe that most of the break through infections will be in the SP and placebo groups and therefore a repeat dose of SP will not be appropriate in this setting where there is a high level of SP resistance.

To ensure that IPTi with any of the study drugs does not lead to a rebound in the incidence of severe malaria or anaemia during the second year of life all infants enrolled in the study will be followed until they reach the age of 24 months. During their second year of life, all episodes of possible malaria or anaemia in infants who present to health centre in the study area will be documented.

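### The t-test fixed for mean Hb leaves the contact 1 Hb unused; Poisson errors should be robust if all malaria episodes count; severe anaemia has no named analysis

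*Protocol*

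**What the plan says.** Section 6 (Data management and analysis) names two methods. For incidence: "The comparison of the incidence of malaria and severe malaria will be analysed using Poisson regression models". For haemoglobin: "The statistical significance of differences in mean Hb will be assessed using t-test". It analyses the two transmission areas as separate trials and argues for a one-sided 5% test. It also promises more detail: "A detailed analytical plan will be prepared and submitted to the DSMB before the study drug codes are broken".

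Section 4.3 defines the primary outcome as "Incidence of clinical malaria: [(history of fever during previous 2 days or axillary temperature >37.5ºC) + parasitaemia of any density", with no other obvious cause of fever, "during the period of 2-11 months of age". It does not say whether a child contributes a first episode or every episode. The only statement that every episode is recorded is in section 4.9 and concerns the second year: "all episodes of possible malaria or anaemia in infants who present to health centre in the study area will be documented".

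Figure 2 lists, at contact 1, "collection of blood samples for Hb and blood film and filter paper". Section 4.5 repeats this for all infants returning for the second DPT/polio dose, the visit at which they are randomised and first treated.

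Severe anaemia (Hb below 7 g/dl) is the second secondary outcome in section 4.3 and is sized in Tables 6a and 6b. Section 6 does not mention it. Severe malaria, which section 6 does mention, is not in the outcome list, but section 4.8 keeps records of admissions for it and section 4.9 follows children for a rebound in it.

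**The concern.** There are three parts, of unequal firmness.

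1. **Hb.** A two-sample t-test cannot use a baseline measurement. The protocol pays for a finger-prick Hb at the randomisation visit and then names a method that ignores it. What is lost is precision on a secondary outcome, chiefly at the smaller site.

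2. **Malaria incidence.** Poisson regression with model-based errors takes the variance of a child's count to equal its mean. If every episode counts and infants differ in underlying risk, counts vary more than that and the standard error of the rate ratio is too small. Some variation in risk is plausible: section 3 reports "significant variation in the prevalence of malaria parasitaemia in <5 year old children at different levels of altitudes", section 4.5 records bednet use, and section 1.6 cites inherited traits that affect malaria. Because the protocol chose 0.05 over the 0.025 level it considered for multiple comparisons, there is no spare margin to absorb inflation.

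3. **Severe anaemia.** An outcome that is both listed and sized has no analysis in the section that assigns analyses.

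**Working it through.** **Reproducing the plan's figures.** With 1 child-year each and variance equal to the mean, n = (1.960 + 0.842)² (r1 + r2)/(r1 − r2)².
- Low site, placebo 0.40 against Lapdap 0.30 (Table 6a): 7.849 × 0.70/0.10² gives 550 (stated 551).
- High site, 0.62 against 0.45 (Table 6b): 7.849 × 1.07/0.17² gives 291 (stated 291).
- A one-sided 5% calculation would give 433 and 229, so the tables are two-sided and allow nothing for variation between children.
- Hb: n = 2 × 7.849 × SD²/d². An SD of 2.0 g/dl, which the protocol does not state, returns the tabled 252 for 0.5 g/dl and 63 for 1.0 g/dl.

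**Hb with and without baseline.** Adjustment multiplies the SD by √(1 − ρ²), where ρ is the correlation between contact 1 and 10-month Hb. The protocol gives no ρ, so a range is assumed. For example, at 291 per arm and ρ = 0 the standard error is 2 × √(2/291) = 0.166, 0.5/0.166 = 3.016, and power is Φ(3.016 − 1.960) = 85.4%.

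| ρ (assumed) | SE reduction | n per arm for 0.5 g/dl | Power, high site (291) | Power, low site (551) |
|---|---|---|---|---|
| 0 | 0% | 252 | 85.4% | 98.6% |
| 0.2 | 2% | 242 | 86.8% | 98.9% |
| 0.3 | 5% | 229 | 88.5% | 99.2% |
| 0.5 | 13% | 189 | 93.6% | 99.8% |

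**Poisson errors if all episodes count.** Follow-up from 2 to 11 months of age is 9 to 10 months, 0.75 to 0.83 year. Mean episodes per placebo child are m = 0.40 × 0.75 to 0.83 = 0.30 to 0.33 (low) and 0.62 × 0.75 to 0.83 = 0.47 to 0.52 (high). Under pure Poisson, the share of episodes that are repeats is 1 − (1 − e^−m)/m: 14-15% at the low site and 20-22% at the high site.

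Let k be the between-child variance of relative risk. It is not in the protocol; 0.5 to 2 is assumed. The count variance is m(1 + km), so with no treatment effect the true standard error is √(1 + km) times the model-based one. The actual error of a nominal one-sided 5% test is 1 − Φ(1.645/√(1 + km)).

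| k (assumed) | SE ratio, low | One-sided error, low | SE ratio, high | One-sided error, high |
|---|---|---|---|---|
| 0 | 1.00 | 5.0% | 1.00 | 5.0% |
| 0.5 | 1.07-1.08 | 6.3-6.4% | 1.11-1.12 | 6.9-7.1% |
| 1 | 1.14-1.15 | 7.5-7.7% | 1.21-1.23 | 8.7-9.1% |
| 2 | 1.26-1.29 | 9.7-10.1% | 1.39-1.43 | 11.8-12.4% |

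For k from 0.5 to 2, a nominal two-sided 5% test would run at 7-13% (low) and 8-17% (high). If only first episodes count, no child contributes a repeat and this inflation does not arise.

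**The case against.** The strongest reply is that most of this is detail that the promised analytical plan may settle. Section 6 names a model family, and robust errors are compatible with it. A rate per child-year fits first episodes over person-time as well as all episodes. That stands: a reader might infer that the primary test is already set to exceed its stated 5%, but the protocol fixes neither the counting rule nor the variance estimator, so it does not support this.

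The evidence for over-dispersion is also indirect. The parasitaemia survey describes variation across altitudes and village groups. Section 3.1 removed two facilities above 800 m from the high-transmission site, and the two areas are analysed separately. Some heterogeneity will remain within a site, but the protocol does not quantify it.

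On Hb, the t-test in a randomised comparison is unbiased and has the right error rate. Section 1.6 already foresees an anaemia analysis adjusted for G6PD deficiency. It would be wrong to read this point as calling the Hb test invalid. What stands is that the method is named outright and leaves out a measurement already planned.

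Finally, a reader might take severe malaria in section 6 for a slip and swap in severe anaemia. Sections 4.8 and 4.9 record severe malaria and give a reason for following it, so the swap would remove an analysis with a stated purpose.

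**Conclusion.** The point holds as an improvement to the analysis wording, not as a demonstrated error in the primary test.

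- **Hb: firm, modest.** The unadjusted t-test is fixed and baseline Hb is collected. The gain is a standard error smaller by 2% to 13% at assumed correlations of 0.2 to 0.5. It matters mainly at the high-transmission site. It rests on the implied SD of 2.0 g/dl and an undocumented correlation between Hb in early infancy and at 10 months.
- **Poisson errors: conditional.** They would be understated, by a factor of 1.07 to 1.43 under no effect, if all episodes count, model-based errors are used and k lies between 0.5 and 2. Remove any one of these conditions and the figures do not apply.
- **Severe anaemia: a plain gap in section 6** for an outcome that the protocol lists and sizes.

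**What to change.** Before the codes are broken, amend section 6 or write into the analytical plan:

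1. Analyse Hb one month after the third course, within each site, by linear regression on arm and contact 1 Hb. Keep infants without a contact 1 value in the analysis by a stated rule.
2. State whether first or all episodes count. If all, keep the Poisson rate ratio with person-time as offset and use robust standard errors clustered on child.
3. Add severe anaemia (Hb below 7 g/dl) to the outcomes analysed by Poisson regression, with the same errors. Leave severe malaria in.

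No extra infants, visits or samples are needed. If there is no over-dispersion, robust errors should change the intervals little. If there is, the intervals widen and the analysis cannot restore the lost power. On the protocol's own one-year, two-sided basis, 80% power for placebo against Lapdap would need 648, 746 or 942 per arm at the low site and 371, 450 or 610 at the high site, for k of 0.5, 1 or 2, against the stated 551 and 291. Mefloquine against placebo, the primary comparison, keeps about 96% power or more throughout that range.
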